### Procedure

All nurses and medical doctors working for CHC organizations in the Dutch region of South Limburg will be asked to participate. After providing informed consent, volunteers will attend a 2-hour long instructional workshop to receive information about the 360ºCHILD-profile, study procedures (inclusion and randomization), and outcome measures.

Participating CHC professionals will identify and approach eligible parents during CHC visits and eligible caregivers at the moment they become involved in the care of the parent’s children. If parents or caregivers are interested and give permission to be contacted by the researcher, researchers will start the information and informed consent procedures and enroll participants in the study after given permission.

At the end of the quantitative phase, quantitative findings will be used for purposive sampling for qualitative research to obtain a variety of perspectives from parents and caregivers and to reach a broad interpretation of the quantitative findings [19,22]. From each group within the study population (parents, adolescents, CHC professionals, and involved caregivers), 2 participants will be invited for each round of interviews. After analysis of the conducted interviews, both quantitative and qualitative findings will be used to select participants for the next round to enrich characteristics and opinions.

### Randomization and Concealed Allocation

After parents sign informed consent, they will be allocated to 1 of 2 parallel groups in a 1:1 ratio (experimental or control group) according to centralized randomization (by an independent administrator based on a protocol). The randomization plan with central block randomization (blocks of 4 and 6) will be generated beforehand by CB (not involved in the enrolment and intervention) using an online randomization system. Each phase (enrolment, randomization, quantitative outcome measurement, and analysis) will be performed independently from the others (concealed allocation), and researchers will be blinded to randomization and allocation. Parents and professionals will be, as much as possible, kept unaware of the detailed study aims related to the allocation.

### Experimental and Control Intervention

For a period of 6 months, children of the participating parents in both groups will receive usual care. Additionally, for 50% of the children (the experimental group), CHC information from the EMD will be electronically transferred to a personalized 360ºCHILD-profile. Directly after baseline measurement, the profile will be available in the EMD for CHC professionals to discuss with the parents or adolescents during the visit. After this visit, the profile also will be made accessible online for the parents or adolescents. During the 6-month follow-up period, participants will be able to consult the profile and use it to contact the caregivers whenever they want. The individual child’s health data, as presented on the profile, will not be collected and used as scientific data in the study. After the last study measurements are completed, a personalized 360ºCHILD profile will also be generated for parents or adolescents in the control group (outside the context of the study). A flowchart of the RCT’s study protocol is provided in Figure 2.

**Figure 2 figure2:**
[figure not shown]
Flowchart of the randomized controlled trial's protocol. CHC: child health care; MD: medical doctor; prof: professional.

### Measures and Measurements

Questionnaires will be used to obtain baseline measurements of the following characteristics: for participating adolescents and children, information on age, gender, and level of functioning and experienced problems as indicated by CHC professionals will be measured; for parents, information on age, gender, country of birth, educational level, perspective on their child’s health and development, parenting situation, and number and age of children will be collected; for CHC professionals and other caregivers, information on discipline, educational level, experience, and perspective on the use of information technologies in health care will be collected.

An overview of the baseline measures regarding population characteristics are presented in Table 1.

**Table 1 table1:** Baseline measures for population characteristics.

Measures	Measuring	Age group	Answer options	Reference
STEP^a^	Standardized professional’s rating of child's functioning, experienced problems, quality of environment, and needed care	0-16	5-point scale	[23]
CGAS^b^	Professional's rating of child's functioning	0-16	Continuous scale	[13,24]
PEDS^c^	Parents’ questions and concerns about child's development	0-6	3-point scale and open ended	[25]
SDQ^d^	Parents’ and adolescents’ perspective on psychological attributes	3-16	3-point scale	[26,27]
NOSIK^e^	Parents’ perspective on parenting stress^f^	2-13	6-point scale	[28]

^a^STEP: Standaard Taxatie Ernst Problematiek (only available in Dutch).

^b^CGAS: Children's Global Assessment Scale.

^c^PEDS: Parents’ Evaluation of Developmental Status.

^d^SDS: Strengths and Difficulties Questionnaire.

^e^NOSIK: Nijmeegse Ouderlijke Stress Index-Korte versie.

^f^As derived from the Parenting Stress Index-Short Form

Measurements will be conducted 6 months after baseline to measure the qualitative and quantitative outcomes of the 360ºCHILD-profile’s and RCT’s feasibility.

#### The 360ºCHILD-profile’s Feasibility

The evaluation of the 360ºCHILD-profile’s feasibility is described in this section. Quantitative outcomes on feasibility will include the following: frequency of use of the 360ºCHILD-profile by CHC professionals during contacts with parents or adolescents, as registered by CHC professionals; the profundity in which the 360ºCHILD-profiles are used during CHC visits, as indicated by CHC professionals on a questionnaire (using questions with answer options on a categorical scale).

Qualitative outcome (semistructured interviews with parents, adolescents, CHC professionals, and other caregivers) will be collected for the follow purposes: to contextualize and further inform the understanding of quantitative findings on 360ºCHILD-profile’s usability; and to explore the expectations of parents, adolescents, CHC professionals, and other caregivers regarding the 360ºCHILD-profile’s potential benefits in CHC practice.

#### RCT Feasibility

Evaluation of the RCT feasibility will occur in both group and is described in this section.

The quantitative measurements will include the following: recruitment rate (the percentages of volunteers versus invited and eligible participants); retention rate (the percentage of participants completing the study versus the participants that started); response rates (the percentages of participants per discipline who filled in and validated the questionnaire versus the number of participants who were requested); compliance to allocated intervention (the percentage of CHC professionals in the experimental group who used the 360ºCHILD-profile during a CHC visit); measure completion (the percentages of completed measures versus incomplete measures and description of missing data); protocol deviations (the description of problems encountered and eventual adaptations to the protocol for properly addressing these problems); health literacy.

Health literacy will be evaluated using the validated Dutch version of the Consumer Quality Index (CQI). The CQI is based on the Consumer Assessment of Healthcare Providers and Systems (CAHPS) and is applicable for parents of children aged 0-18 year who visit CHC [29]. The validated CQI includes questions about accessibility, ability to understand, completeness and applicability of received care, and health information and advice, with answer options on a 2-, 3-, or 4-point scale (subscale reliability: Cronbach α=.75-.82) [30]. Additionally, relevant questions from “Supplemental Items for the CAHPS on Health Information Technology” were translated from English to Dutch and incorporated into the CQI questionnaire [31]. The research team developed additional questions to ensure measurement of all dimensions of the construct’s “access to healthcare and health information” [32]. The dimensions we indicated as relevant for the CHC context and this study are availability, accommodation, accessibility, and acceptability. Affordability is not relevant in this context because CHC care is offered for free to all children and parents. This set of additional questions (n=6) with answers options on a 5-point scale will be used for the first time, and no information on the diagnostic parameters is available yet.

The qualitative measurements for RCT feasibility will include semistructured interviews with parents, adolescents, CHC professionals, and other caregivers, and will be performed for the following purposes: to contextualize and further inform the quantitative findings on recruitment, retention and response rates, compliance to allocated intervention, measurement completion, and health literacy; to explore CHC professionals’ experiences during recruitment of parents and adolescents, and participants’ satisfaction regarding their study participation and allocated intervention and perspective on requirements for a future randomized trial.

All semistructured interviews will be in person and audio-recorded. Recordings will be transcribed, and the collected data will be coded (participants will be allocated a participant number code to relate data to this code). Records will be stored in a locked place on the server separate from the other study data. Only the investigator collecting the data will have access to this documentation.

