### Study Population and Sample Size

The study population will mainly consist of parents and CHC professionals (nurses and medical doctors) who are involved in the care of the parent’s child (age 0-16 years) experiencing emerging problems. Adolescents (age >11 years) and other involved caregivers can also be included as participants, but children under the age of 12 years will not themselves participate. If parents or adolescents cannot comprehend the written health information (due to a language barrier or other reasons), they will not be included in this study.

For the quantitative phase, we aim to recruit 30 parents, 30 CHC professionals, 10 adolescents, and 10 other caregivers. For feasibility studies, in which outcome parameters like recruitment, response rates, and variance in the outcomes of questionnaires (SD) are measured, a sample size of 60-70 participants is justified [16,20,21]. For qualitative research with purposive sampling, it is estimated that saturation will be reached after including 20-30 participants (7-10 participants per target population; ie, parents and CHC professionals) [19,22].

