#### Quantitative Outcome Data

Descriptive analysis will be performed to present outcomes on the 360ºCHILD-profile’s and RCT’s feasibility (usability). The descriptive analysis of the 360ºCHILD-profile will include the following: the frequency in which the 360ºCHILD-profile is used, for which the mean and variability will be calculated; and the profundity of use of the 360ºCHILD-profile during a CHC visit, which will be presented as proportions per category.

The descriptive analysis for RCT feasibility will include the following: recruitment, retention, and response rates, compliance to allocated intervention, measurement completion, and missing data, which will be presented as logistic data and proportions; protocol deviations, which will be described using text; outcome on health literacy, including descriptions for the total sample and for each group, with continuous measures (presented as mean, SD, and CI) and categorical measures (presented as proportions).

Statistical between-group analysis will be performed to preliminarily calculate (estimates of) differences between groups (and 95% CIs), using linear mixed models. Potential confounders (for example health status, age, and education) will be evaluated and, if necessary, adjusted.

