From a pragmatic viewpoint, we searched for design options that fit current research questions and CHC context. A mixed methods design with a sequential explanatory (quantitative–qualitative) setup was chosen to enable testing our a priori, practice-based hypotheses and to give voice to parents, adolescents, and caregivers to refine theory. The pragmatic approach of the feasibility RCT enables the execution of a randomized trial within the preventive and multidisciplinary field of work and generation of results that fit this context [17]. The investment of time by CHC professionals is limited as much as possible; only a short training period is needed, each professional will need to recruit only 1-2 parent(s), and professionals are left close to daily practice during the “intervention” period (care as usual). Furthermore, CHC professionals in the experimental group do not have to drastically change their working method; they will present the personalized profile to parents and adolescents, but after that, all participants are free in choosing how (often) to use it. The between-group difference might seem rather subtle, but we expect it will have substantial impact. Our hypothesis is that the availability of the dashboard will automatically lead to efficiency (there is less wasting of time to search for data in the EMD and better quality of health literacy and early prevention of disease progression). Moreover, we expect that the theoretical structure of the profile will intuitively guide clinical reasoning in line with the context of CHC and PHC.

Information bias will be reduced by the centralized randomization, blinding of researchers for randomization, and keeping participants unaware of the detailed study aims.

Children and their parents have been chosen as the level of randomization (and not CHC professionals) to avoid bias due to differences in professionals’ working methods, characteristics, and level of experience. Contamination is avoided by virtue of the fact that, for CHC professionals in the control group, it is not possible to obtain an overview of the holistic health data from the EMD, as it is simply not available.

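### Compliance with the allocated intervention is a percentage of professionals, but parents and children are randomised, so its denominator is not a trial arm and may misstate uptake

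*Protocol article*

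**What the plan says.** Under RCT Feasibility, the protocol article lists compliance with the allocated intervention among the quantitative outcomes and defines it as "the percentage of CHC professionals in the experimental group who used the" profile during a visit. The Quantitative Outcome Data section reports it with the other rates, as proportions.

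The unit of allocation is stated elsewhere. Randomization and Concealed Allocation says: "After parents sign informed consent, they will be allocated to 1 of 2 parallel groups in a 1:1 ratio (experimental or control group"). The plan there is "central block randomization (blocks of 4 and 6"), and no stratification by professional is mentioned. The section on the experimental and control interventions describes the experimental group as half of the children. The Discussion is explicit: "Children and their parents have been chosen as the level of randomization (and not CHC professionals").

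On numbers, Study Population and Sample Size says "we aim to recruit 30 parents, 30 CHC professionals, 10 adolescents, and 10 other caregivers". The Discussion adds that "each professional will need to recruit only 1-2 parent(s"). It also refers to professionals in the experimental group and in the control group, as though each professional belonged to one arm.

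**The concern.** The compliance rule presupposes an experimental group of professionals, and the design does not create one. A professional who recruits two parents can have none, one or two children in the experimental group. With one child in each arm, that professional belongs to both groups or to neither, and the article gives no rule. The definition also does not say how to score a professional who used the profile for only one of two experimental children. On the natural reading, any use counts as compliant.

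Compliance with allocation is a named objective of the RCT feasibility evaluation, and the Introduction says the study should build a rationale for later effect studies, including sample size. For that purpose the useful quantity is the share of allocated children who actually received the intervention contrast. The health literacy comparison is between randomised parents, and a percentage of professionals does not sit on the same unit.

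**Working it through.** The article gives no compliance target or expected value, so there is no figure to reproduce. The check asks how far the professional-level figure can lie from the child-level one.

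**Inputs from the article:** 30 parents, 1:1 allocation (taken as 15 and 15), one or two parents per professional.

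**Assumptions, not in the article:** use per experimental child p = 0.4, 0.6 or 0.8; correlation of use between two children of one professional ρ = 0, 0.5 or 1; block structure ignored; any use counts; one recruiting professional per child.

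**Step 1: where two parents of one professional fall.**
- One in each arm: 2 × 15 × 15 / (30 × 29) = 450/870 = 52%.
- Both experimental: 15 × 14 / (30 × 29) = 210/870 = 24%.

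If 15 professionals each recruited two parents, the expected numbers are 7.8 mixed, 3.6 experimental only and 3.6 control only. Counting each professional in every arm where they have a child gives 11.4 + 11.4 = 22.8 memberships for 15 people. These are not two separate groups.

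**Step 2: chance that a professional scores as compliant.** With one experimental child it is p. With two it is 2p − [p² + ρp(1 − p)]. At p = 0.6 this gives 0.84, 0.72 and 0.60 for ρ = 0, 0.5 and 1.

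**Step 3: professional-level figure at p = 0.6** (expected compliant professionals divided by expected professionals with at least one experimental child).

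| Professionals with two parents | With ≥1 experimental child | With two experimental children | ρ = 1 | ρ = 0.5 | ρ = 0 |
|---|---|---|---|---|---|
| 0 | 15.0 | 0 | 60.0% | 60.0% | 60.0% |
| 5 | 13.8 | 1.2 | 60.0% | 61.1% | 62.1% |
| 10 | 12.6 | 2.4 | 60.0% | 62.3% | 64.6% |
| 15 | 11.4 | 3.6 | 60.0% | 63.8% | 67.6% |

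Last row, ρ = 0: (7.76 × 0.60 + 3.62 × 0.84) / 11.38 = 67.6%. In the same row, p = 0.4 gives 47.6% and p = 0.8 gives 85.1%.

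**Step 4: the direction is not fixed.** Keep 15 professionals with two parents each. Suppose those with two experimental children always use the profile and those with one use it 40% of the time.
- Child level: (2 × 3.62 + 0.4 × 7.76) / 15 = 69.0%.
- Professional level: (3.62 + 0.4 × 7.76) / 11.38 = 59.1%.

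Here the professional-level figure is too low.

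**Step 5: an upward extreme.** Eight professionals hold all 15 experimental children (seven with two, one with one) and each uses the profile for one child. The professional figure is 8/8 = 100%; the child figure is 8/15 = 53%.

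**The case against.** The phrase can be read sensibly as professionals caring for at least one experimental-group child. On that reading it is a legitimate measure of delivery, because professionals are the ones who present the profile. Baseline data are split by randomised group only for parents, adolescents and children, so the article does not treat professionals as an arm there. Targets of 30 parents and 30 professionals allow one parent each, and then the two figures coincide. Frequency and profundity of use are reported separately, and counting rules may stand in the full protocol.

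Much of this stands. The professional-level figure is worth keeping, and the numerical effect may be small or nil. It does not remove the conflict, however. The article does not leave the definition out; it states one, on a unit that it says elsewhere was not randomised, and it expressly allows two parents per professional. A mean frequency of use does not give the proportion of allocated children whose profile was used.

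A reader might go further and infer that uptake will be overstated. The article does not support that. Inflation needs professionals with two experimental children who use the profile for only one of them. A professional with one child in each arm has a single experimental child and adds no inflation, so the 52% in Step 1 shows that membership is ambiguous, not that the rate is biased. The 0.84 in Step 2 applies only to professionals with two experimental children and assumes independent use. All-or-none use gives no inflation, and Step 4 shows that the sign can reverse.

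**Conclusion.** The point holds as a mismatch of unit. Compliance with allocation is defined over a group that randomisation does not form, and the rule for a professional with two children is missing from the stated definition. The figure may therefore misstate the share of allocated children whose profile was used.

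The misstatement is plausibly upward where professionals hold two experimental children. At an assumed 60% use per child, the professional-level figure is between 60% and about 68%, and the upper end requires 15 professionals with two parents each and independent use. It is zero with one experimental child per professional and can be negative. All these sizes rest on assumed use rates and correlations.

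Severity is moderate. The outcome is descriptive, with no threshold or progression rule attached, and nothing in the article says this percentage will set the dilution assumed in a later trial. The figure should nevertheless match the randomised comparison that the study is meant to inform.

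**What to change.** Define compliance as the number of children allocated to the experimental group whose profile was used in at least one CHC visit during the 6 months, divided by all children allocated to that group, with an exact 95% CI. Keep the professional-level percentage as a secondary description, with its denominator stated as professionals caring for at least one experimental-group child.

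The change is one definition. Professionals already register use, but each registration must be linked to the child's study number, and the article does not say that it is. The figure may look less favourable. It will also be imprecise: with 15 children, 12 of 15 (80%) would have an exact 95% CI of 52% to 96%. That reflects the sample size and should be visible in the report.

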### Statistical Analysis

Baseline characteristics of all participants will be presented using descriptive statistics (mean, SD, or frequencies and range) in a table. Data of parents, adolescents, and children will be presented for the total group and for both randomized groups separately.

#### Quantitative Outcome Data

Descriptive analysis will be performed to present outcomes on the 360ºCHILD-profile’s and RCT’s feasibility (usability). The descriptive analysis of the 360ºCHILD-profile will include the following: the frequency in which the 360ºCHILD-profile is used, for which the mean and variability will be calculated; and the profundity of use of the 360ºCHILD-profile during a CHC visit, which will be presented as proportions per category.

The descriptive analysis for RCT feasibility will include the following: recruitment, retention, and response rates, compliance to allocated intervention, measurement completion, and missing data, which will be presented as logistic data and proportions; protocol deviations, which will be described using text; outcome on health literacy, including descriptions for the total sample and for each group, with continuous measures (presented as mean, SD, and CI) and categorical measures (presented as proportions).

Statistical between-group analysis will be performed to preliminarily calculate (estimates of) differences between groups (and 95% CIs), using linear mixed models. Potential confounders (for example health status, age, and education) will be evaluated and, if necessary, adjusted.

